---

# 1. INTRODUCTION AND RATIONALE OF THE STUDY

## 1.1 Background

Naloxone is a mu-opioid-receptor (MOR) antagonist drug, which dose-dependently exhibits hypoalgesic and hyperalgesic properties [1]. Naloxone (and other MOR-antagonists) have been used in research to study the role of endogenous opioids on central processing of pain. It has been hypothesized that the endogenous opioid modulation of pain is impaired or altered in chronic pain conditions [2–5]. In a previous study using an electrical pain model on human patients, naloxone (21 microg/kg) increased the established area of secondary hyperalgesia [6]. Further, administration of naloxone and naltrexone to animals following resolution of an inflammatory condition, have demonstrated a reinstatement of hypersensitivity to noxious stimulus, indicating latent sensitization [7–9]. It has thus been speculated that endogenous opioids may play an important role in the transition of acute to chronic pain in humans [7,8,10].

Recently, we were unable to show reinstatement of secondary hyperalgesia after resolution of a burn-injury by administering naloxone in a low dose (21 microg/kg) (H-2-2012-036) [11]. Based on these findings we hypothesized, that the negative results may be due to the low dose of naloxone or insufficient tissue injury to generate latent sensitization.

The systemic doses of opioid antagonists used in animal studies to demonstrate latent sensitization have been 0.3 to 3.0 mg/kg of naltrexone [7] or 3-10 mg/kg of naloxone [12]. Further, high doses of 1-2 mg/kg of naloxone have been used in clinical and experimental psychiatric, endocrinological, neurological and nutritional studies in patients [13–18] and in healthy individuals [19–23]. In one pain related study, 6 mg/kg of naloxone was given to healthy patients intramuscularly [24]. Only mild to moderate, transitory side-effects were recorded in these studies.

We therefore initiated another translational study in which we hypothesized that a higher dose of naloxone (2 mg/kg) would reinstate secondary hyperalgesia in human patients following resolution of a mild burn-injury and thus show latent sensitization in humans. We demonstrated in 4 out of 12 patients, that naloxone administered 7 days after a mild burn injury was associated with reinstatement of secondary hyperalgesia [12]. This study thus raises two important questions: *first*, is it possible to foresee individuals who will demonstrate latent sensitization upon challenge with an injury, and, *second*, will challenge with a larger tissue injury, including more extensive inflammatory reactions, induce a higher relative number of responders.

Consequently, our aim in the present study, is twofold. *First*, to investigate if naloxone will reinstate clinical pain and hyperalgesia after resolution of a more pronounced inflammatory injury in a postsurgical model, i.e., three to four weeks after a unilateral, impacted mandibular third molar extraction procedure. At this time point, patients are expected to be pain free at rest and only have mild pain during specific movements. We expect in this way to contribute with further knowledge on the role of the endogenous opioid-system in latent sensitization, following a mild thermal injury and clinically relevant surgery-related tissue injury. *Second*, in volunteers, to investigate if high-sensitizers (*a priori* developing large areas of secondary hyperalgesia after exposure to a mild burn-injury) are more prone

to demonstrate latent sensitization following naloxone administration, than low-sensitizers (*a priori* developing small areas of secondary hyperalgesia).

The post-surgical pain model, used in the present study, induces deep tissue inflammation and is associated with an increased degree of nociception compared to the superficial burn-injury model, used in our previous studies (H-2-2012-036, H-2-2012-174). In the animal studies on latent sensitization, deep tissue inflammation was induced by plantar incision [7] or injection of complete Freud's adjuvant (CFA) [9]. A pain model, which induces moderate deep tissue inflammation, like post-groin hernia repair (GHR; ongoing study ) or post-impacted mandibular third molar extraction (TME; present study), might thus be necessary to generate latent sensitization in humans. The GHR-procedure involves surgical injury to densely innervated soft tissues, and postoperative pain likely, in addition to the inflammatory component, also includes a neuropathic component. Since, the TME-procedure involves damage to the mucoperiosteal tissues, it is of importance to detect if latent sensitization is operative in a predominantly inflammatory pain model [25], compared to the GHR-procedure, a mixed neuropathic and inflammatory pain model. This distinction seems relevant since chronic pain states, from a pathophysiological perspective, are separated into neuropathic, inflammatory or mixed conditions.

In regard to the risk of development of a sustained pain state after the naloxone administration in individuals after TME, we consider it highly unlikely. *First*, naloxone does not affect the production of endogenous opioids, but only acts as a short-acting reversible antagonist of opioids. *Second*, in adults the distribution half-life ( $T_{1/2\alpha}$ ) of naloxone is 40 to 70 seconds [26], and the elimination ( $T_{1/2\beta}$ ) half-life, 54 to 64 min [26] [27]. Naloxone has not any known long-acting metabolites and thus there are no pharmacokinetic reasons for a prolonged reversal of endogenous opioids. *Third*, in studies with rodents, administration of naltrexone or naloxone has caused transient episodes of hypersensitivity with duration of 60 to 90 min [9]. Repeated administration of naltrexone, over the course of months, has confirmed full reversibility of the hypersensitivity episodes. *Fourth*, in our recent patient-study with high dose naloxone (H-2-2012-174) in 4 of 12 individuals responding to naloxone, very short lasting changes in hypersensitivity were seen [12]. Thus it is our strong belief that the likelihood of development of significant or serious adverse effects, including sustained pain, is minimal in this study.

## 2. AIM

The principal aims of the study are:

\* *first*, to investigate whether the administration of naloxone, a selective mu-opioid receptor (MOR) antagonist, can re-introduce clinical pain (at rest, during movement and in pressure-evoked condition) and hyperalgesia three to four weeks after a unilateral, mandibular third molar extraction procedure (TME).

\* *second*, to assess predictability of the latent sensitization response, assessed as naloxone-induced reinstatement of secondary hyperalgesia after resolution of an experimental burn-injury, according to individual sensitization phenotype (high-sensitizers vs. low-sensitizers).

## 3. OUTCOMES

### 3.1 Primary Outcome

#### 3.1.1 Impacted mandibular third molar extraction (TME) study

- A composite measure of pain (numerical rating scale [NRS]; 0 = no pain; 10 = worst perceivable pain) during rest + masticatory pain + pain during external algometry (100 kPa) at the injury site, assessed 4 weeks ( $\pm$  3 days) after uncomplicated extraction of an impacted mandibular third molar.

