- The examiner fills out the Clinical Opiate Withdrawal Scale (COWS)
- Brief medical examination (only Day 1):
  - Medical history
  - Auscultation of heart and lungs
  - Blood pressure and heart rate
  - Routine palpation of lymphatic nodes in the submandibular regions, the supraclavicular fossae and the axillae.
  - Assessment of deep tendon reflexes
- Urine-sample to test for opioids (sample is discarded just after the analysis).
- Randomization (consecutively by pre-specified randomization)
- Monitoring with three-lead ECG and measurements of pulse oximetry, blood pressure and respiratory rate is started.
- Baseline assessments are performed at **time – 20" to – 8"** (Fig. 2):
  - Reaction time assessed as Online Reaction Time.
  - Pain rating (0-10, NRS) at rest in the supine position.
  - Pain rating (0-10, NRS) during a standardized mastication procedure.
  - Pain rating (0-10, NRS) during pressure-algometry applied perpendicularly at the mandibular skin sites overlying the surgical area and the contralateral mirror-site.
  - Secondary hyperalgesia/allodynia at surgical site and contralateral mirror-site at the mandibular skin sites overlying the surgical area and the contralateral mirror-site.
- **Time 0" to 25": First** step target-controlled-infusion (TCI; including a bolus dose) of naloxone/placebo infusion (**Fig. 2**)
- **Time 13" to 15":** The examiner assesses COWS-rating

- **Time 15'' to 25''**: Identical assessments as made at baseline are repeated
- **Time 25'' to 50''**: **Second** step TCI (including a bolus dose) of naloxone/placebo infusion (**Fig. 2**)
- **Time 37'' to 39''**: The examiner assesses COWS-rating
- **Time 39'' to 49''**: Identical assessments as made at baseline are repeated
- **Time 50'' to 75''**: **Third** step TCI (including a bolus dose) of naloxone/placebo infusion (**Fig. 2**)
- **Time 63'' to 65''**: The examiner assesses COWS-rating
- **Time 65'' to 75''**: Identical assessments as made at baseline are repeated
- **Time 75''**: End of naloxone/placebo infusion
- Monitoring data are continuously registered and documented
- Potential side-effects are continuously registered and documented
- **Time 75'' – 180''**: observation period where the participant is allowed to drink, eat and begin to ambulate. Monitoring is continued until 100''
- **Time 180''**: the participant is discharged

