#### 9.2.4 Pain assessments

##### 9.2.4.1 TME-participants

Pain assessments are performed in three different situations:

- \* Pain rating (0-10, NRS) at rest in the supine position
- \* Pain rating (0-10, NRS) during a standardized mastication procedure. Pain is evaluated by asking the participant to chew a preparedD chewing gum (between the upper and lower, first molar of the surgical side during 30 seconds at a cycles of 40 Hz controlled by a iPhone-driven metronome (app. Steinway

---

D

Musical Instruments 1.1.4). Volunteers will be instructed that each chewing cycle ends when the upper and lower teeth clench and this time-point should be synchronized with the metronome. Volunteers will then rate the maximum pain intensity evoked by the task.

The sugar-free chewing gum (V6; Mondelez, Denmark) is prepared by the participant by chewing on the gum in 2" immediately at the start of the examination day. The gum is thereafter kept in a plastic container and re-used by the participant during the mastication procedure.

\* Pain rating (0-10, NRS) during a pressure stimulus (100 kPa) applied perpendicularly at the mandibular skin sites overlying the surgical area and the contralateral mirror-site, using a pressure algometer (Somedic AB, Hörby, Sweden) with a 1-cm^2 felt-tipped probe, directed at the point of maximum pain. During the measurement, the investigator will stabilize the lower jaw by sliding the gloved, index finger along the internal side of the body of the mandible, while applying lateral indirect pressure (100 kPa), externally to the relaxed masseter muscle. The participants rate the maximal, experienced pain intensity (0-10 NRS).

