#### *9.2.6 Pressure pain threshold (TME-participants)*

Pressure pain threshold (PPT) will be assessed using an electronic pressure algometer (Algometer, Somedic AB, Sweden). The pressure algometer employs a 1-cm^2 circular probe, which is applied manually, perpendicularly to the skin with increasing pressure at a rate of 1-2 kPa/s. The assessment area will include the point of maximum pain. PPT assessments will be performed at baseline (-20 min to -8 min; Fig. 2) and during infusions (15 min to 25 min; 39 min to 49 min; 65 min to 75 min) at the surgical site and at the mirror-site in the contralateral groin. The participants interrupt the stimulation by pushing a button when the pressure becomes painful, and the investigator then stops the stimulation. The cut-off value is 350 kPa. Values exceeding the cut-off are designated 351 kPa.

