### 13. STATISTICAL ANALYSES

#### 13.1 Sample size calculations

##### 13.1.1 TME-participants

Sample size calculations are based on following assumptions and estimations (abbreviations: BL = baseline; NX = naloxone; PL = placebo; TCI = during target-controlled-infusion):

1. a primary outcome based on a summed measure (SM) of resting pain (RP), masticatory pain (MP; (movement-related) and pressure-evoked pain (PM; pressure algometry [100 kPa]).  $NRS_{SM} = NRS_{RP} + NRS_{MP} + NRS_{PM}$ .
2. the summed pain intensities (SPIs) are calculated as: (BL-SPINX) and (TCI-SPINX), and, (BL-SPIPL) and (TCI-SPIPL), where (TCI-SPI) indicates SM-value at highest obtainable TCI-step (Fig. 2).
3. the summed pain intensity differences (SPIDs) are the differences: **SPIDNX** = (TCI-SPINX) – (BL-SPINX) and **SPIDPL** = (TCI-SPIPL) - (BL-SPIPL)

4. the mean [SD] BL-pain intensities are estimated to be: resting pain 1 [1] NRS-units; movement related pain 2 [2] NRS-units; pressure evoked pain 4 [2] NRS-units.
5. the mean [SD] summed BL-pain intensity (BL-SPI) is estimated to be 7 [4.1] NRS-units (Table 2).
6. the minimal relevant SPID-difference, calculated as  $\Delta SPID = SPID_{NX} - SPID_{PL}$  is estimated to be 5 (NX-group: RP = 4; MP = 5; PM = 7 [total 16]/PL-group: RP = 2; MP = 4; PM = 5 [total 11]) corresponding to a  $\Delta SPID\% = 45\%$ .
7. the design is a placebo-controlled, randomized, double-blind, crossover study
8. the significance level  $\alpha$  is set to 0.01 and the power is set to  $= 0.90$  ( $\beta = 0.10$ )

The total number of individuals estimated to be included in the study is calculatedE to be 14 (effect size 1.2). Using the range of variances in Table 2, it can be calculated that the number of individuals ranges from 9 to 19, with effect sizes of 1.7 to 1.0, respectively.

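### The third-molar primary composite has no site control, so a general naloxone effect on evoked pain cannot be told from injury-related reinstatement; separately, one mirror-site is given as the groin

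*Protocol*

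**What the plan says.** Protocol section 3.1.1 defines the TME primary outcome as the sum of three 0-10 ratings: rest, mastication and "pain during external algometry (100 kPa) at the injury site". Section 13.1.1 writes the same sum with no contralateral term. Section 13.2.1 analyses the naloxone-minus-placebo difference in change from baseline (ΔSPID) across infusion steps. Its mixed model lists step, drug, hyperalgesia area, pressure pain threshold and two psychometric scores, but no side factor.

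Contralateral data are collected. The baseline list in section 9.1.1 includes "Pain rating (0-10, NRS) during pressure-algometry applied perpendicularly at the mandibular skin sites overlying the surgical area and the contralateral mirror-site", and the baseline assessments are repeated at each of the three infusion steps. Section 9.2.4.1 describes the same two-sided measurement. The contralateral rating has no place in sections 3.1.1, 3.2.1 or 13.2.1. The monofilament area on both sides is a secondary endpoint in section 3.2.1, but no comparison between sides is defined.

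The pressure pain threshold is a different measurement. Section 9.2.6 takes it "at the surgical site and at the mirror-site in the contralateral groin".

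Section 1.1 says that naloxone "dose-dependently exhibits hypoalgesic and hyperalgesic properties".

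**The concern.** The first aim, read with section 1.1, concerns latent sensitization left by the surgical injury. Two of the three components of the sum are provoked during the infusion, by chewing and by pressure. If naloxone raises sensitivity to such stimuli everywhere, the sum rises at the injury site although the injury played no part.

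Randomised placebo removes effects of time, procedure and expectation. It does not remove a general effect of the drug, which is present on one day and absent on the other. A positive result would then be ambiguous in exactly the respect the study is meant to settle. The ambiguity would carry into the comparison that section 1.1 draws with the hernia-repair model.

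**Working it through.** **1. Reproduce the plan's figure.** Inputs from section 13.1.1: component SDs 1, 2 and 2; correlation 0.5; target difference 5; alpha 0.01; power 0.90.

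- Variance of the sum = 1 + 4 + 4 + 2 × (1 + 1 + 2) = 17, so SD = 4.12.
- Standardised difference = 5 / 4.12 = 1.21.
- A paired t-test with two-sided alpha 0.01 (noncentral t) gives n = 14, power 0.914.
- Effect sizes 1.7 and 1.0 give 9 and 19.

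All three match the protocol, so no stated figure is wrong. Like the plan, this uses the baseline SD of the sum as the SD of the within-subject drug difference.

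**2. Split the target by component** (naloxone 4, 5, 7; placebo 2, 4, 5).

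| Component | Difference | Mirror-site rating? |
|---|---|---|
| Rest | 4 − 2 = 2 | No |
| Mastication | 5 − 4 = 1 | No, surgical side only |
| 100 kPa pressure | 7 − 5 = 2 | Yes |
| Total | 5 | 2 of 5 points can be checked |

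**3. What the contrasts identify.** For the pressure rating, let t be the change from time and procedure, g a general naloxone effect and s an effect specific to the injured side, all additive.

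- Injury site: naloxone t + g + s, placebo t. Difference: g + s.
- Mirror-site: naloxone t + g, placebo t. Difference: g.
- Drug-by-side contrast: (g + s) − g = s.

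The composite sees only g + s. If sensitization spreads to the other side by an amount c, the contrast becomes s − c and is conservative.

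**4. What the primary test does if s = 0.** Paired t-test, n = 14, two-sided alpha 0.01, SD 4.12 (the range is for SD 5.0 to 3.0, the ends of Table 2). The sizes of g are assumed; the protocol gives none.

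| Wholly non-specific rise in the sum | Chance of a positive result |
|---|---|
| 1 point | 4% (3% to 7%) |
| 2 points | 16% (10% to 35%) |
| 3 points | 42% (27% to 75%) |
| 5 points | 91% (75% to 99.7%) |

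**5. Precision of the side contrast.** Assume an effect of 2 and an SD of 2 per side, borrowed from the planning value "pressure evoked pain 4 [2] NRS-units". The SD of the contrast is 2 × √(2(1 − r)), where r is the correlation between sides and is not given in the protocol. For 90% power at two-sided alpha 0.01:

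- r = 0.25: SD 2.45, n = 26
- r = 0.50: SD 2.00, n = 19
- r = 0.75: SD 1.41, n = 11

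With 14 evaluable subjects the contrast is adequately powered only if the two sides are closely correlated.

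**6. The groin.** Sections 9.1.1, 9.2.4.1 and 9.2.5.1 all name a contralateral mandibular mirror-site; section 9.2.6 alone names the groin. The threshold is not part of the sum in sections 3.1.1 and 13.1.1. It appears only as a factor in the mixed model of section 13.2.1, with no side stated.

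**The case against.** The composite measures the three pain conditions named in aim 1, so it does not contradict its aim. How collected side data are contrasted is often left to an analysis plan, which is not shown here. Both points are fair, and they are why the primary test can stand. But the protocol itself fixes the primary outcome and its formula to the injury site, and gives the mirror-site rating no purpose.

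The evidence for a general hyperalgesic effect is also mixed. Section 1.1 names both hypoalgesic and hyperalgesic properties. The enlargement at 21 microg/kg concerned an area already established in an electrical pain model, and another study at that dose showed no reinstatement. The effect is therefore possible but not shown.

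Four stronger readings are tempting and not supported:

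- A reader might infer that the groin error damages the primary outcome. It cannot, because the threshold lies outside the composite.
- A reader might infer that no contralateral data have any role. The contralateral monofilament area is a secondary endpoint; the gap is the 100 kPa rating and the absence of any side contrast.
- A reader might take the evoked share of the target, (1 + 2) / 5 = 60%, or the dose ratio 3.25 / 0.021 ≈ 155, as the size of the bias. Neither estimates it. The first is a planning split that includes chewing pain, itself a symptom of interest. The second compares different pain models and implies a dose-response that the document does not give.
- A reader might want the side contrast to decide whether the primary result counts. It covers one component, may be underpowered and is biased by contralateral spread. It could also favour the injured side if naloxone merely amplifies residual pain that starts higher there.

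**Conclusion.** The concern holds as a limit on attribution. The composite has no within-subject site control, so it cannot separate a general naloxone effect on evoked pain from injury-related reinstatement, and the placebo day does not help. The available control covers 2 of the 5 target points. The size of any general effect is unknown, and the rejection rates in the working are illustrations that rest on assumed rises and on the plan's own SDs. The sample size is not in question.

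The groin wording is a separate error in an operative methods section. Followed literally, it leaves the threshold without a valid mirror-site.

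**What to change.** Keep the primary test unchanged. Pre-specify as supportive the drug-by-side contrast for the 100 kPa rating: the change at the injury site minus the change at the contralateral site on naloxone, minus the same quantity on placebo. Do likewise for the monofilament area. Report each with its confidence interval beside the primary result. State in advance that a similar rise on both sides would not support attribution to the injury, and that the contrast informs interpretation without acting as a pass/fail condition.

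In section 9.2.6 replace the groin with the contralateral mandibular mirror-site used elsewhere in the protocol.

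The cost is wording and two paired contrasts on data already scheduled, with no new procedure. The limits to state alongside are that rest and mastication remain unchecked, that power at 14 subjects is limited, and that the contrast is conservative if sensitization spreads to the other side.

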#### 3.1.2 Burn injury (BI) study

- Areas of secondary hyperalgesia assessed by a weighted-pin instrument (256 mN) 0, 1, 2 and 165-169 hrs (during TCI [time; 10-15"A; 44-49"; and 70-75"]) after the BI.

### 3.2 Secondary Endpoints

#### 3.2.1 Impacted mandibular third molar extraction (TME) study

- Secondary hyperalgesia/allodynia area at mandibular skin sites directly overlying surgical and contralateral side (nylon monofilament (nominal value 4.93 [bending force: mean + SD = 69  $\pm$  14 mN])
- Online Reaction Time (<http://getyourwebsiteherecom/jswb/rttest01.html>)
- Hospital Anxiety and Depression Scale (HADS; only pre-infusion)
- Pain Catastrophizing Scale (PCS; only pre-infusion)
- Clinical Opiate Withdrawal Scale (COWS; cf. p. 31 to 32)

#### 3.2.2 Burn injury (BI) study

- Pain during BI (NRS)
- Pin-prick pain thresholds assessed (PPT) by weighted-pin instruments at primary and secondary hyperalgesia areas (0, 1, 2, 165 and 165-169 hrs (during TCI [time; 15-25"; 44-49"; and 70-75"]) after BI
- Online Reaction Time (<http://getyourwebsiteherecom/jswb/rttest01.html>)

---

A The double prime characters (") indicate min.

- Hospital Anxiety and Depression Scale (HADS; only pre-BI)
- Pain Catastrophizing Scale (PCS; only pre-BI)
- Clinical Opiate Withdrawal Scale (COWS; cf. p. 31 to 32)

## 4. ETHICAL CONSIDERATIONS

### 4.1 General ethical considerations

The study will be conducted in accordance to the principles of the Helsinki Declaration with updated amendments.B The protocol will be submitted for approval to the Regional Committee of Research Ethics, Danish Health and Medicines Authority and the Danish Data Protection Agency. Investigators will also report significant or major changes to the protocol to these agencies. The study will be registered in EUDRACT and the international database [www.clinicaltrial.gov](http://www.clinicaltrial.gov).

Comparable studies have previously been approved of the Regional Committee of Research Ethics of the Capital Region (H-2-2012-174; H-15002712), the Danish Health and Medicines Agency (2012-005663-17; 2015-000793-36) and the Danish Data Protection Agency (2013-41-1475; RH-2014-30-1150, I-Suite nr.: 02815). These studies were also registered in ClinicalTrials.gov (NCT01992146) and EudraCT (2012-005663-27 DK 20130222; 2015-000793-36 DK 20150216; 2015-000815-42 DK 20150216).

